### Blinding

The pharmaceutical company staff will not participate in the trials, and the investigator, physicians, nurses, outcome measurement operative, statisticians, and the participants will be blinded to the group information until the end of the trial, when all statistical analyses are finished.

### Outcome measures

#### Primary outcome measure

The primary outcome measure will be as follows: (1) the progression of ACR 50 after 1, 2, and 3 months of treatment compared to baseline; (2) the change in DAS28 before and after 1, 2, and 3 months of treatment; and (3) the difference between the two groups in the van der Heijde modified Sharp score before and after 12 months of follow up.

The ACR50 is a scale to measure change in RA symptoms [15, 16]. The ACR50 requires the following: 50% or greater improvement in tender joint count, 50% or greater improvement in swollen joint count, and at least 50% improvement in three of the following five measurements: (1) assessment of the patient’s arthritis pain using a visual analogue scale (VAS) of 0–100 mm, (2) global assessment of the patient’s disease activity using a VAS (0–10), (3) assessment of the patient’s physical function and disability using the HAQ-DI, (4) an acute-phase reactant value such as erythrocyte sedimentation rate (ESR), or (5) C-reactive protein (CRP) level. ACR20 and ACR70 (measured as ≥ 20% improvement and ≥ 70% improvement, respectively) are required in the tender joint count, swollen joint count, and in 3 of the other 5 measurements [16].

Although compared to ACR50 and ACR70, ACR20 has been accepted as the efficacy benchmark in RA clinical trials and has greater discriminant capacity to distinguish patients on active treatment from placebo control [15, 17, 18], we choose ACR50 as the primary outcome measure because ACR50 is a more desirable target for patients and provides useful information in addition to ACR70 [19, 20].

The DAS28 is widely used as an indicator of RA disease activity and response to treatment, and clinical trials have used DAS28 to assess treatment effect [14, 21]. The formula for DAS 28 is:$$ 0.56\times \sqrt{28\ \mathrm{painful}\ \mathrm{joint}\ \mathrm{count}}+0.28\times \sqrt{28\ \mathrm{swollen}\ \mathrm{joint}\ \mathrm{count}}+0.70\times \left(\mathrm{in}\ \mathrm{ESR}\right)+0.014\times \mathrm{GH}. $$

The 28 joints are 10 proximal interphalangeal joints and 10 proximal interphalangeal joints of the hands and wrists, elbows, knees, and shoulders bilaterally. GH is patient general health measured by VAS (0–100 mm); “0” is the best and “100” is the worst [16, 22–24].

The van der Heijde modified Sharp score is the radiographic assessment of the *erosion* and *the joint narrowing* in the 10 metacarpophalangeal joints, 8 proximal interphalangeal joints, 10 metatarsophalangeal joints, and 2 interphalangeal joints of the big toes. In addition, erosion is also assessed in the two interphalangeal joints of the thumbs, first metacarpal bone, radius, ulnar bones, trapezium and trapezoid, navicular bones, and right and left lunate bones bilaterally, whereas joint narrowing is also assessed in the third, fourth, and fifth carpometacarpal joints, multiangular-navicular joints, capitate-navicular-lunate joints, and right and left radiocarpal joints bilaterally. The maximum erosion score in the hand is 5, and in the foot it is 10, according to the degree of erosion. Thus, the maximum number of erosions in the hand is 160, and in the feet it is 120. The grade of joint space narrowing is as follows:1 = focal or doubtful2 = general, less than 50% of the original joint space3 = general, more than 50% of the original joint space or subluxation4 = no joint space remaining, luxation, or ankylosis

Therefore, the maximum score for joint space narrowing is 120 in the hand and 48 in the feet. The van der Heijde modified Sharp score is the sum of the erosion and joint space narrowing score [16, 25].

The ACR50 and DAS28 will be estimated at baseline and after 1, 2, and 3 months of treatment, and at the 6-month and 12-month follow up. The van der Heijde modified Sharp score will be measured only at baseline and after 12 months.

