**Methods/design:**

We will conduct a multicenter, randomized, double-blind, placebo-controlled clinical trial to determine whether the traditional Chinese medicine Juanbi pill could relieve joint pain in RA and protect the joints. A total of 120 patients with active RA will be enrolled and treated with the Juanbi pill or a placebo for 3 months. The primary outcome measures are as follows: rate of in the American College of Rheumatology (ACR)50, change in the 28-joint Disease Activity Score (DAS28) from baseline at beginning of therapy to 3 months, and a change in the van der Heijde modified Sharp score measured from baseline to 12 months. The secondary outcome measures are as follows: rate of change in ACR20, ACR70, Health Assessment Questionnaire-Disability Index (HAQ-DI), and change in score in the Patient Assessment of Arthritis Pain, Patient Global Assessment of Arthritis, and the Athens Insomnia Scale (AIS) from baseline to 2-week, 1-month, 2-month, 3-month, 6-month, and 12-month follow up. In addition, the rate of change (score) in the ACR50 and DAS28 from the baseline to 2-week, 1-month, 2-month, 6-month, and 12-month follow up are also the secondary outcome measures.

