#### Secondary outcome measures

The secondary outcome will be to compare the rate of change in the ACR20/70, HAQ-DI, Patient Assessment of Arthritis Pain, Patient Global Assessment of Arthritis, and AIS from baseline to 2 weeks, 1 month, 2 months, 3 months, and at the 6-month and 12-month follow up. The rate of change in the ACR50 and DAS28 from t baseline to 2 weeks, 1 month, 2 months, and 6-month and 12-month follow up are also secondary outcome measures, and the change in score on the 36-item Short-Form Health Survey Questionnaire (SF-36) from baseline to 1 month, 2 months, 6 months, and 12 months is also calculated.

The HAQ-DI is a subscale of the ACR20/50/70. It is a completely patient-reported outcome, bridged between biochemical and physical measurements, and widely used in RA clinical trials to assess the disease activity and the patient’s disability [26]. The HAQ-DI measures eight dimensions of functional activity, including dressing, rising, eating, walking, hygiene, reach, grip, and usual activities. Each item is graded by four degrees, and scored from 0 to 3. A score 0 means without any difficulty, 1 means with some difficulty, 2 means with much difficulty, and 3 means unable to do the activity. The score in the HAQ-DI is the sum of each item averaged as an overall HAQ-DI score of 0–3. Only when at least six of the eight dimensions are answered is the scale valid. Generally, an HAQ-DI score 0–1 represents mild to moderate difficulty, 1–2 represents moderate to severe disability, and 2–3 represents severe to extreme disability [27]. Patient Assessment of Arthritis Pain and Patient Global Assessment of Arthritis are two subscales of the ACR20/50/70 and are measured by a VAS of 0–100 mm and of 0–10 cm, respectively [16].

Patients with RA often have sleep disturbance, and the more severe the disease, the more severe the sleep problems [16, 28]. The AIS, a self-assessment psychometric instrument that was designed to quantify sleep difficulty, consists of eight items, including sleep induction, awakenings during the night, final awakening, total sleep duration, sleep quality during the night, wellbeing during the night, functioning capacity during the day time, and sleepiness during the day time. Each item is scored from 0 to 3, the higher score representing poor sleep quality. The scale maximum is 24 [29].

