### Sample size calculation

We calculated the sample size according to our primary study. We conducted a preliminary experiment from December 2015 to May 2016 into the efficacy of the Juanbi pill combined with MTX versus MTX alone, and we found that patients taking the Juanbi pill combined with MTX achieved 84.8% ACR50, whereas patients in the MTX group achieved 55.5% ACR50 response. According to the formula of the rate in completely random design:$$ \mathrm{n}1=\mathrm{n}2=\frac{\left[{u}_{\alpha /2}\sqrt{2\overline{p}\left(1-\overline{p}\right)}+{u}_{\beta}\sqrt{p_1\left(1-{p}_1\right)+{p}_2\left(1-{p}_2\right)}\right]\ }{{\left({p}_1-{p}_2\right)}^2}, $$

where n_1_ and n_2_ are the number of participants in the Juanbi and placebo groups, respectively, and *u*_*α*/2_=1.96 when type 1 error is 0.05, *u*_*β*_ = 1.282 when type II error is 0.1 in two-sided tests: $$ \overline{p} $$ is the mean of *p*_1_ and *p*_2_ [31]. It was estimated that approximately 50 participants per group were needed to achieve 90% power and a (two-sided) 5% significance level in detecting treatment differences. Thus, the final sample size has been set at a total of 120 patients (60 in each group), considering a 20% dropout rate. Forty participants (20 in the treatment group and 20 in the placebo group) from the three centers will be recruited.

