### Statistical analysis

Efficacy and safety analyses will be conducted according to the intention-to-treat principle. The method of last observation carried forward will be applied in analysis of missing values. All statistical analyses will be performed using Statistical Packages of Social Sciences software (SPSS) (version 21.0). A *p* value < 0.05 will be defined as a statistically significant result. Means and standard deviations will be used to describe the continuous variables, such as demographic and clinical outcome variables, whereas percentages will be used for categorical variables such as the rate. Continuous variables following the normal distribution will be analyzed by Student’s *t* test; otherwise, non-parametric tests will be used to compare group differences.

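### The protocol gives two incompatible sets of primary comparisons, seven or three, with no success rule, and is sized for one ACR50 comparison only

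*Protocol article*

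**What the plan says.** All references are to the protocol article.

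- **Primary outcome measure.** Three items are listed. The first two start "the progression of ACR 50 after 1, 2, and 3 months of treatment compared to baseline; (2) the change in DAS28", the second reading in full "the change in DAS28 before and after 1, 2, and 3 months of treatment". The third is "the difference between the two groups in the van der Heijde modified Sharp score before and after 12 months of follow up". A later paragraph of the same section calls ACR50 the primary outcome, in the singular, when explaining why it was preferred to ACR20.
- **Abstract, Methods/design.** The primary DAS28 outcome is "change in the 28-joint Disease Activity Score (DAS28) from baseline at beginning of therapy to 3 months". Month 3 is explicit for DAS28 and implied for ACR50, because the abstract's secondary list gives every other visit for both measures. The Sharp score at 12 months is the third primary.
- **Secondary outcome measures.** "The rate of change in the ACR50 and DAS28 from t baseline to 2 weeks, 1 month, 2 months" and the later follow-up visits are named as secondary.
- **Statistical analysis.** The only decision rule is that a p "value < 0.05 will be defined as a statistically significant result".
- **Sample size calculation.** One contrast is used, ACR50 of 84.8% against 55.5%, from which "approximately 50 participants per group were needed to achieve 90% power and a (two-sided) 5% significance level". The visit to which those rates belong is not stated. No effect size or standard deviation is given for DAS28 or the Sharp score.

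**The concern.** Four comparisons (ACR50 and DAS28, each at months 1 and 2) are both primary and secondary in the same document. After unblinding, either definition could be cited as the prespecified one, so the timepoint that carries the claim could be chosen on the data.

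The second problem is that several primaries are named, one blanket threshold applies to each, and the text never says what pattern of results makes the trial positive. The 5% and 90% in the sample size section belong to one ACR50 test. Once more than one primary is kept, at least one of these figures no longer describes the trial's overall claim. Which one depends on a rule that the protocol does not give.

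**Working it through.** **1. Count the primaries.** Primary outcome measure section: 3 (ACR50) + 3 (DAS28) + 1 (Sharp) = 7. Abstract: 1 + 1 + 1 = 3. The difference of 4 is exactly the set that the Secondary outcome measures section calls secondary.

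**2. Reproduce the sample size.** Inputs from the sample size section: p1 = 0.848, p2 = 0.555, mean 0.7015, normal quantiles 1.96 and 1.282. Using the pooled formula with the numerator squared (the square is absent in the printed formula):

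n = [1.96·√(2·0.7015·0.2985) + 1.282·√(0.848·0.152 + 0.555·0.445)]² / 0.293² = [1.268 + 0.786]² / 0.0858 = 49.2, rounded up to 50.

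This matches the stated 50, and 50 × 1.2 = 60 gives the stated enrolment. Power at 50 per group is 90.5%. The calculation is therefore right for one ACR50 comparison.

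**3. If any one primary suffices, each tested at 0.05.** Under independence, family-wise error = 1 − 0.95^k.

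- k = 3: 1 − 0.857 = 14.3%.
- k = 7: 1 − 0.698 = 30.2%.

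For jointly normal two-sided test statistics these are upper limits whatever the correlation (Šidák's inequality). The documents give no correlations. I assumed 0.3–0.8 between visits, 0.3–0.7 between ACR50 and DAS28, and 0–0.2 with the Sharp score. Simulation with 1,000,000 draws per setting then gives about 13–14% for three tests and 20–28% for seven.

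**4. If all primaries must succeed.** Error is at most 5%. Joint power cannot exceed that of the least-powered endpoint. It cannot be computed, because DAS28 and the Sharp score have no planning inputs.

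**5. If alpha is split (Bonferroni).** Power = Φ{[0.293·√n − z·√(2·0.7015·0.2985)] / √(0.848·0.152 + 0.555·0.445)}, where z is the two-sided critical value:

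| ACR50 power | alpha 0.05 | 0.05/3 = 0.0167 | 0.05/7 = 0.0071 |
|---|---|---|---|
| 50 per group | 90.5% | 80.3% | 70.5% |
| 60 per group | 94.9% | 88.0% | 80.6% |

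The 60-per-group row applies if everyone enrolled is analysed, as intention to treat with last observation carried forward would allow. Carried-forward values may dilute the effect, so that row is the favourable end. Holding 90% power would need 64 per group for a three-way split, or 64/0.8 = 80 after allowing for 20% dropout.

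**The case against.** The best defence has four parts.

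- **The success rule is not in the text.** A reader might infer that a p value below 0.05 on any one of seven comparisons makes the trial positive. No section says so: the Statistical analysis section defines when a result is called significant, not when the trial succeeds. This stands, so the 14.3% and 30.2% are conditional figures.
- **Error and power do not fail together.** A reader might also infer that both the 5% and the 90% are lost. With each test at 0.05, no single success rule does that. If any one suffices, error inflates, but the chance of success is at least that of ACR50 alone. If all are required, power falls, but error is protected. This stands too.
- **Three is the likelier count.** The abstract and the secondary outcome section agree, and only the primary outcome section differs. That makes seven the worst case. It does not remove the contradiction.
- **A multiplicity rule may sit in an analysis plan that is not shown.** This is fair as to a missing adjustment. It does not cover a protocol that defines its primary comparisons in two ways, since any analysis plan would have to override one of them.

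The singular reference to ACR50 does not settle the matter. It explains the choice among ACR thresholds, and the list above it, the abstract and the Discussion all treat ACR50, DAS28 and the Sharp score as the main measures.

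**Conclusion.** The point holds as a contradiction about which comparisons are primary, combined with an unstated success rule. The sample size figure itself is sound for one ACR50 test.

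The size of the problem depends on the rule adopted. Under any-one-suffices, family-wise error is at most about 14.3% on the three-primary reading and 30.2% on the seven-primary reading, with somewhat lower values under the assumed correlations. Under all-required, error is controlled, but the power of the joint claim is unknown. Under a three-way alpha split, ACR50 power drops by about 10 percentage points at 50 per group and about 7 at 60. The power figures assume that the preliminary response rates are true and apply at the tested visit.

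This should be corrected before unblinding, because until then the confirmatory claim is not uniquely defined.

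**What to change.** - Correct the Primary outcome measure section so that ACR50 and DAS28 at months 1 and 2 are secondary, in line with the abstract and the Secondary outcome measures section.
- Name ACR50 response at month 3 as the single primary outcome, since ACR50 response is the endpoint type used for sizing. State that timepoint in the sample size section, after confirming that the preliminary rates refer to it.
- Test DAS28 change at month 3, then Sharp score change at month 12, in that fixed order. Each is tested at two-sided 0.05 only if the preceding test succeeded.
- Label all other p values descriptive.

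This holds family-wise error at 5% across the sequence and keeps the ACR50 power calculation without an alpha penalty or extra patients. Co-primaries or an alpha split would also be valid, but each would need a new sample size justification.

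The cost is a formal amendment to a trial that has been recruiting since December 2016. The Blinding section keeps allocation concealed until the analyses are finished, so the change can still be made without knowledge of results. The other cost is that DAS28 and the Sharp score cannot be claimed as confirmatory if ACR50 fails, nor the Sharp score if DAS28 fails.

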#### Secondary outcome measures

The secondary outcome will be to compare the rate of change in the ACR20/70, HAQ-DI, Patient Assessment of Arthritis Pain, Patient Global Assessment of Arthritis, and AIS from baseline to 2 weeks, 1 month, 2 months, 3 months, and at the 6-month and 12-month follow up. The rate of change in the ACR50 and DAS28 from t baseline to 2 weeks, 1 month, 2 months, and 6-month and 12-month follow up are also secondary outcome measures, and the change in score on the 36-item Short-Form Health Survey Questionnaire (SF-36) from baseline to 1 month, 2 months, 6 months, and 12 months is also calculated.

The HAQ-DI is a subscale of the ACR20/50/70. It is a completely patient-reported outcome, bridged between biochemical and physical measurements, and widely used in RA clinical trials to assess the disease activity and the patient’s disability [26]. The HAQ-DI measures eight dimensions of functional activity, including dressing, rising, eating, walking, hygiene, reach, grip, and usual activities. Each item is graded by four degrees, and scored from 0 to 3. A score 0 means without any difficulty, 1 means with some difficulty, 2 means with much difficulty, and 3 means unable to do the activity. The score in the HAQ-DI is the sum of each item averaged as an overall HAQ-DI score of 0–3. Only when at least six of the eight dimensions are answered is the scale valid. Generally, an HAQ-DI score 0–1 represents mild to moderate difficulty, 1–2 represents moderate to severe disability, and 2–3 represents severe to extreme disability [27]. Patient Assessment of Arthritis Pain and Patient Global Assessment of Arthritis are two subscales of the ACR20/50/70 and are measured by a VAS of 0–100 mm and of 0–10 cm, respectively [16].

Patients with RA often have sleep disturbance, and the more severe the disease, the more severe the sleep problems [16, 28]. The AIS, a self-assessment psychometric instrument that was designed to quantify sleep difficulty, consists of eight items, including sleep induction, awakenings during the night, final awakening, total sleep duration, sleep quality during the night, wellbeing during the night, functioning capacity during the day time, and sleepiness during the day time. Each item is scored from 0 to 3, the higher score representing poor sleep quality. The scale maximum is 24 [29].

The SF-36 consists of 36 items and measures eight dimensions, which are physical functioning, bodily pain, general health perceptions, physical role functioning, emotional role functioning, social role functioning, and mental health [16]. The SF-36 is a patient-reported survey of patient health and is widely used in the assessment of the life quality of patients with RA [16, 30]. In addition, concomitant medication is recorded as a secondary outcome.

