## Methods/design

### Study design

This study is a multicenter, randomized, double-blinded, placebo-controlled clinical trial with two parallel arms (Fig. 1). The aim of the study is to evaluate whether the Juanbi pill combined with MTX is effective for the management of active RA. In total, 120 patients with active RA will be recruited (60 patients per arm) from centers in Shanghai, China, from Longhua Hospital affiliated with Shanghai university of Traditional Chinese Medicine, Yueyang Integrated Medicine Hospital affiliated with Shanghai University of Traditional Chinese Medicine, and Shanghai Guanghua Hospital of Integrated Traditional Chinese and Western Medicine. The Standard Protocol Items: Recommendation for Interventional Trials (SPIRIT) 2013 checklist is shown in Additional file 1.

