This study is designed to answer whether the Juanbi pill combined with MTX is preferred in the treatment of active RA, compared with MTX alone. If this trial succeeds, it will provide the patients and physicians an option of combining the Juanbi pill with MTX to obtain better disease remission. Moreover, this trial will provide data about the effect of the Juanbi pill on joint pain and function, quality of life, and safety. The results will aid clinical decision-making for the management of active RA and will provide useful information that can be incorporated into future guidelines.

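### The only separate joint-pain score is a secondary outcome compared at six visits, none of them decisive, among about 50 secondary comparisons under one unqualified p < 0.05 rule

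*Protocol article*

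**What the plan says.** The Abstract (Methods/design) says the trial is "to determine whether the traditional Chinese medicine Juanbi pill could relieve joint pain in RA and protect the joints". The Study design section gives a broader aim: "The aim of the study is to evaluate whether the Juanbi pill combined with MTX is effective for the management of active RA".

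Under Primary outcome measure there are three outcomes: ACR50, DAS28 and the van der Heijde modified Sharp score. None is a pain score. Pain does enter two of them:

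- ACR50 requires improvement in tender joint count, and the pain VAS is one of five further components of which three must improve.
- The DAS28 formula contains the painful joint count.

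Under Secondary outcome measures the article says: "The secondary outcome will be to compare the rate of change in the ACR20/70, HAQ-DI, Patient Assessment of Arthritis Pain" and further scales, "from baseline to 2 weeks, 1 month, 2 months, 3 months, and at the 6-month and 12-month follow up". For the pain score the list runs "Patient Assessment of Arthritis Pain, Patient Global Assessment of Arthritis, and AIS from baseline to 2 weeks, 1 month, 2 months, 3 months", followed by the 6-month and 12-month visits. ACR50 and DAS28 come back from "baseline to 2 weeks, 1 month, 2 months, and 6-month and 12-month follow up are also secondary outcome measures". SF-36 is added at four visits.

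The Statistical analysis section has one rule for all of this: "A *p* value < 0.05 will be defined as a statistically significant result". The Discussion announces that "this trial will provide data about the effect of the Juanbi pill on joint pain and function, quality of life, and safety".

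**The concern.** The article states a pain question and promises pain evidence, but it does not say which comparison answers the question. A reader who applies the significance rule as printed may call the pain score significant at 2 weeks, at any of months 1, 2 and 3, or at months 6 and 12, when treatment has been over for 3 and 9 months. Two analysts with the same data could differ on whether pain showed a significant effect, depending on the visit they quote. The same holds for function (HAQ-DI at six visits) and quality of life (SF-36 at four).

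At stake is the error rate behind any pain, function or quality-of-life statement. One p < 0.05 suggests 5%, but the chance that something in the set reaches it is higher. The validity of the trial and of its primary outcomes is a separate matter and is not affected by this point.

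**Working it through.** **The plan's own figure.** The article gives no error rate for the secondary outcomes. Its only computed design figure is the ACR50 sample size: 84.8% vs 55.5%, two-sided 5%, 90% power. With the numerator squared, (1.96·√(2·0.7015·0.2985) + 1.282·√(0.848·0.152 + 0.555·0.445))² / 0.293² = 49.2, so 50 per group, as stated. The 5% in that calculation belongs to one ACR50 comparison. It does not cover a set of secondary comparisons.

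**Count of secondary comparisons** (from Secondary outcome measures):

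- ACR20, ACR70, HAQ-DI, pain, patient global and AIS at 2 weeks and 1, 2, 3, 6 and 12 months: 6 × 6 = 36, of which 6 are on pain.
- ACR50 and DAS28 at 2 weeks and 1, 2, 6 and 12 months: 2 × 5 = 10.
- SF-36 at 1, 2, 6 and 12 months, taken as one score: 4.
- Total: 36 + 10 + 4 = 50.

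If the eight stated SF-36 dimensions are tested separately, the total is 36 + 10 + 32 = 78. ACR50 and DAS28 at months 1 and 2 are also listed as primary, so 2 × 2 = 4 comparisons have a double status. Without them the count is 46.

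**Error rates under no effect.** The article gives no correlations, so they are assumed. For k equicorrelated normal statistics with common correlation ρ, each tested at two-sided 0.05:

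P(at least one) = 1 − E_u{[Φ((1.96 − √ρ·u)/√(1−ρ)) − Φ((−1.96 − √ρ·u)/√(1−ρ))]^k}, with u standard normal.

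At ρ = 0 this is 1 − 0.95^k. For a false result in favour of Juanbi only, the second Φ term is dropped. At ρ = 0 that gives 1 − 0.975^k, and the benchmark for a single test is 2.5%.

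| Assumed ρ | Pain, 6 tests, either direction | Pain, 6 tests, false benefit | All 50 tests, either direction |
|---|---|---|---|
| 0 | 26.5% | 14.1% | 92.3% |
| 0.5 | 20.7% | 10.4% | 62% |
| 0.7 | 16.4% | 8.2% | 40% |
| 0.8 | 13.9% | 6.9% | 30% |
| 0.9 | 10.8% | 5.4% | 19% |

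The expected number of false positives does not depend on correlation: 50 × 0.05 = 2.5, or 78 × 0.05 = 3.9. With 46 comparisons the chance of at least one is 60% at ρ = 0.5, little different from 62%.

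**Relative size.** For pain in either direction, 10.8/5 = 2.2 and 26.5/5 = 5.3 times nominal. For a false benefit, 5.4/2.5 = 2.2 and 14.1/2.5 = 5.6 times. With one named visit, the pain comparison returns to 5% two-sided.

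**The case against.** The strongest reply is that the ordering of secondary outcomes is commonly left to a statistical analysis plan or full protocol, and neither is shown. The word secondary already ranks these outcomes below the primaries. The p < 0.05 sentence can be read as a generic definition, and the article nowhere says that one visit out of six suffices for a pain claim. Part of this stands: the missing hierarchy alone would be a weak point. But the article is not silent. It fixes a rule without exception, lists the outcomes by visit, and announces evidence on pain, function and quality of life. The text as printed therefore permits the selective reading, even though it does not require it.

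Several stronger readings are tempting, and the documents do not support them:

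- A reader might infer that the pain question rests only on the secondary pain score. It does not, because tender or painful joint counts enter two primary outcomes. What is true is that no primary measures pain on its own, and that an ACR50 response is possible without improvement in the pain VAS.
- A reader might take pain as the trial's one question. The abstract sentence also names joint protection, which the Sharp score addresses, and Study design and the Discussion put the aim more broadly.
- A reader might state a fourfold error rate for pain, or that a false positive among the 50 is more likely than not. The first is the ρ = 0.5 case only. The second fails by ρ = 0.7 (40%). Repeated changes on one VAS share a baseline, and last observation carried forward raises their correlation further, so the lower rows of the table deserve weight.
- The either-direction figures include false harm. For a claim of benefit, 5% to 14% against 2.5% is the right comparison.

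**Conclusion.** The point holds in this form: a separate joint-pain score compared at six visits with none decisive, one unqualified significance rule over about 50 secondary comparisons, and planned statements on pain, function and quality of life. The inflation for pain is at least about twofold at every assumed correlation from 0 to 0.9 and reaches more than fivefold under independence. The result for all 50 comparisons depends much more on the correlation (19% to 92%), and its upper end is a bound, because the scales are related and ACR20 and ACR70 share components. The figures rest on equal correlation, normal test statistics and no true effect on any outcome. This should be corrected because it limits what can be claimed from the secondary outcomes; it does not undermine the trial as a whole.

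**What to change.** In Secondary outcome measures and Statistical analysis:

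1. Name the between-group difference in change in Patient Assessment of Arthritis Pain from baseline to month 3, the end of treatment, as the single decisive pain comparison (key secondary), tested at two-sided 0.05.
2. State that all other secondary outcomes and visits are exploratory, reported as estimates with 95% confidence intervals and not called statistically significant.
3. Limit the statements on pain, function and quality of life in the Abstract and Discussion accordingly.

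Making the pain test conditional on a positive primary result is optional. It is not possible as the text stands: there are three primary outcomes, and the Abstract gives ACR50 and DAS28 at 3 months, while Primary outcome measure gives them at 1, 2 and 3 months and Secondary outcome measures lists months 1 and 2 again. Those sections would first have to be reconciled to one defined primary analysis.

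The change needs no patients, visits or data. Its cost is that isolated p < 0.05 results at other visits or on other scales can no longer be claimed as findings.
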